## Methods

### Study design

We will conduct a two-armed randomized controlled trial (RCT). Participants will be randomly assigned to one of two conditions: Family Connections (FC) or Treatment As Usual (TAU). Block randomization will be carried out among the three clinical centers, considering that if a patient has more than one family member who attends the group, they will be randomized together to be included in the same condition. Measures will be taken before starting the intervention, after the intervention, and at the 6-month follow-up to determine whether improvements after the intervention are maintained in the long term. The study flowchart appears in Fig. 1. We will follow the CONSORT statement (Consolidated Standards of Reporting Trials, http://www.consort-statement.org) [31, 32] and the SPIRIT guidelines (Standard Protocol Items: Recommendations for Interventional Trials) [33, 34].

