### Sample size

To determine the sample size, the effect sizes found in the literature on the subject have been considered. The controlled study by Grenyer et al. [35], which tested a group psychoeducation protocol for caregivers of people with BPD, reported medium to large effect sizes (dyadic adjustment, *d* = .78; family empowerment, *d* = 1.4). In addition, on measures of burden, Grenyer [35] reported significant improvements between post assessment and the 12-month follow-up, with medium effect sizes (Burden Assessment Scale, *d* = .45). These effects are consistent with the literature on psychological treatments for other psychiatric disorders, such as the meta-analysis of psychological interventions for caregivers of people with bipolar disorders (Burden, *g* = −.80) [36].

Taking these data into account, in the present study, adopting a conservative approach, an effect size of 0.60 is expected because our design includes two experimental conditions. Considering an alpha of 0.05 and a statistical power of 0.80 on a 2-tailed *t* test, the total sample size needed to reach an effect size of 0.60 for burden is 90 participants (45 participants per experimental condition). To control the maximum possible loss of participants during treatment, based on the literature about programs for family members of patients with BPD, a 29% dropout rate is expected [20, 23–25, 27]. Thus, the required sample size should be a total of 116 participants (58 participants per group). These calculations were made with the software program G*Power 3.1 [37].

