### Data analyses

In order to analyze whether there are differences between the experimental conditions before the application of the treatment, Student’s t tests will be performed for the continuous variables, and chi-square tests for the categorical variables. To compare the effectiveness of the two treatment conditions, we will perform a multivariate analysis of variance for repeated measures (MANOVA) for the variables with subscales, and ANOVA for the single variables, taking the pretreatment, posttreatment and follow-up moments as within-subject factor and the treatment condition (FC vs TAU) as between-subject factor.

Moreover, between-group changes will be computed by calculating standardized effect sizes (Cohen’s d). Finally, we will perform zero-order correlations and linear regression analyses between the measures of the caregivers and the measures of the patients.

Because the trial is still going on, the state of the art in analytic methodology for RCT will be reviewed before analyzing the data, and so variations in the selection of the most appropriate analytic procedures may occur.

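### The planned FC–TAU comparison uses baseline as an outcome occasion and omits centre; this is valid but generally less efficient than a baseline-adjusted contrast, and it is not the t test behind the 80% power

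*Protocol article*

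**What the plan says.** - **Efficacy model (Data analyses).** The within-subject factor has three levels: pretreatment, post-treatment and follow-up. The only between-subject term is "the treatment condition (FC vs TAU) as between-subject factor". No covariate or centre term is named. The section does not say whether the condition effect or the time × condition interaction is the efficacy test, or which visit is primary.
- **Baseline tests (Data analyses).** t tests and chi-square tests are planned "In order to analyze whether there are differences between the experimental conditions before the application of the treatment".
- **Randomisation (Study design).** "Block randomization will be carried out among the three clinical centers".
- **Sample size.** "Considering an alpha of 0.05 and a statistical power of 0.80 on a 2-tailed" t test, with "an effect size of 0.60 is expected because our design includes two experimental conditions"; the total needed "for burden is 90 participants (45 participants per experimental condition").
- **Hypotheses (Background).** Hypothesis (a) is that both arms improve and that the gains last to 6 months. Hypothesis (b) is that FC outperforms TAU on burden, family functioning and other measures.
- **Reservation.** The Data analyses section ends by saying that methods will be reviewed before analysis and may change.

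**The concern.** Baseline BAS and FAD-GFS are scheduled for every caregiver (Table 1), and centre is known for everyone. A comparison that conditions on baseline uses that information fully. A comparison that treats baseline as one more outcome occasion generally uses it less well.

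The planned model offers two tests that involve condition. The interaction has 2 degrees of freedom and does not by itself give one FC–TAU difference at a stated time. The condition main effect averages in the pretreatment value, where no effect can exist. Neither is the single two-group comparison that was powered, so the stated 80% describes neither. Leaving out centre also means that the analysis does not reflect how participants were randomised.

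The baseline significance tests add nothing: under randomisation, any difference between arms before treatment is due to chance.

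**Working it through.** **Inputs from the Sample size section.** Two-sided alpha 0.05, d = 0.60, n = 45 per arm.

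**Assumptions not in the document.** SD of 1 at each visit; the same correlation rho between any two visits (compound symmetry), from 0.3 to 0.7; a true difference of 0, 0.60 and 0.60 SD at the three occasions; independent participants. The calculation is for a single score analysed by ANOVA; the MANOVA version was not calculated.

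**Step 1: the plan's own figure.** For a two-sample t test the noncentrality is 0.60 × √(45/2) = 2.846 on 88 df, which gives power 0.804. With 44 per arm it is 0.795. The plan's 45 per arm is reproduced.

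**Step 2: time × condition, 2 df.** The differences 0, 0.6, 0.6 have mean 0.4. The squared deviations sum to 0.16 + 0.04 + 0.04 = 0.24. Noncentrality = (45/2) × 0.24/(1 − rho) = 5.4/(1 − rho), on 2 and 176 df.

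**Step 3: condition main effect, 1 df.** The mean difference is 0.4, and the variance of a person's three-visit mean is (1 + 2rho)/3. Noncentrality = (45/2) × 0.16/[(1 + 2rho)/3] = 3.6/[(1 + 2rho)/3], on 1 and 88 df.

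**Step 4: baseline-adjusted contrast at one later visit.** The residual variance is 1 − rho². Noncentrality = 2.846/√(1 − rho²), on 87 df.

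| rho | Step 2 noncentrality | time × condition power | Step 3 noncentrality | condition main effect power | Step 4 noncentrality | adjusted contrast power |
|---|---|---|---|---|---|---|
| 0.3 | 7.71 | 0.69 | 6.75 | 0.73 | 2.98 | 0.84 |
| 0.4 | 9.00 | 0.76 | 6.00 | 0.68 | 3.11 | 0.87 |
| 0.5 | 10.80 | 0.84 | 5.40 | 0.63 | 3.29 | 0.90 |
| 0.6 | 13.50 | 0.91 | 4.91 | 0.59 | 3.56 | 0.94 |
| 0.7 | 18.00 | 0.97 | 4.50 | 0.56 | 3.98 | 0.98 |

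At rho 0.8 the interaction and the adjusted contrast both exceed 0.99.

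**Step 5: why adjustment gains.** Like for like at one visit, a comparison of change from baseline has variance 2(1 − rho), against 1 − rho² after adjustment. The ratio is 2/(1 + rho): 1.54, 1.33 and 1.18 at rho 0.3, 0.5 and 0.7. It exceeds 1 for every rho below 1.

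**Step 6: sensitivity to the effect pattern.** If the effect halves by follow-up (0, 0.60, 0.30), interaction power runs from 0.56 to 0.91 over the same rho range. The adjusted contrast at post-treatment is unchanged.

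**Step 7: centre.** If centre explained 1%, 5% or 10% of the variance (assumed), power of the t test would move from 80.4% to 80.7%, 82.3% or 84.3%.

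**The case against.** **The size rests on a correlation that the document does not give.** This stands. At rho 0.6 and 0.7 the interaction has 0.91 and 0.97 against 0.94 and 0.98. BAS asks about the past 6 months, so the recall windows at baseline and post-treatment may overlap, and low correlation cannot be taken for granted.

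**The main effect may not be the intended test.** This also stands. The section never names it as the efficacy test and later refers to between-group changes, which points to the interaction. Its power of 0.73 falling to 0.56 applies only if that term is read as the test.

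**Baseline is already used.** A reader might infer that baseline serves only the significance tests between arms. The model does not support that: pretreatment is a level of the time factor, and the interaction compares change from baseline. Baseline differences are subtracted, though less efficiently than by covariate adjustment.

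**The pretreatment occasion is needed.** Hypothesis (a) concerns change within each arm. An analysis restricted to the two later visits would not test it, so any fix has to keep that comparison.

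**Covariates may be left to an analysis plan, and the article reserves changes.** This is only partly persuasive. The article does more than stay silent: it writes out the factors and the role of baseline. The reservation names no covariate, centre term or contrast.

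**Centre adds little precision.** Probably true, as step 7 shows. The wording on blocking is also brief; blocking by centre is its natural reading but is not spelled out.

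**Conclusion.** The point holds as one of efficiency and of mismatch with the sample size calculation. The planned model is valid, and no bias is shown. Under the stated assumptions the loss in power against a single-visit adjusted contrast is 0.15 at rho 0.3 (0.84 − 0.69), 0.06 at rho 0.5 (0.90 − 0.84) and about 0.01 at rho 0.7 (0.98 − 0.97).

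A reader might infer that the trial is underpowered because the analysis differs from the t test. The documents do not support that. The interaction passes 80% somewhere between rho 0.4 and 0.5 if the effect is sustained, and only the main effect lies below 80% throughout the range. What can be said is that the stated 80% would match the planned test only by coincidence.

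The absolute powers are optimistic for every method. They assume independent participants, whereas relatives of one patient are randomised together and treatment is given in groups.

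**What to change.** - **Hypothesis (b).** Estimate the FC–TAU difference at post-treatment and at 6 months, adjusted for baseline score, with centre as a fixed effect. Use ANCOVA, or a mixed model with baseline means constrained equal across arms. Name one of the two contrasts as the primary test.
- **Hypothesis (a).** Keep the change from pretreatment to post-treatment and to follow-up within each arm. The constrained-baseline mixed model serves both hypotheses.
- **Centre.** Include it because the analysis should reflect the randomisation, not for a large gain in power.
- **Baseline tests.** Replace the t and chi-square tests with a descriptive table by arm.

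No new data are needed. The cost is a little extra analysis work and one design decision, since the article designates no primary time point. The Data Availability section says the trial is still recruiting, so this can be fixed before any data are analysed.

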## Discussion

FC is an intervention program for relatives of people with BPD that has been adapted to Spanish by our research team. FC was designed to train relatives of people with BPD to improve global family functioning, empowerment, resilience, validation, and mindfulness skills, and decrease grief, burden, hopelessness, and psychological symptoms [25].

The first aim of this study is to provide data from an RCT about the efficacy of this intervention protocol in a Spanish sample of participants consisting of family members of patients with BPD who are treated at clinical centers specializing in the treatment of this disorder, compared to an active condition (TAU). A second objective is to study the acceptability (expectations and opinions) of this program among the participants. Another aim is to analyze whether there are changes in relatives’ burden and psychological symptoms related to the improvement observed in patients. The fourth aim consists of studying whether these changes are related to the family climate. Finally, we will examine the opinions and perceptions of relatives and patients about both intervention protocols.

The study aims to contribute to the existing literature on the efficacy and effectiveness of intervention programs for relatives of BPD patients, specifically FC. In addition, it aims to assess whether the improvements obtained in the relatives are related to those obtained by the patients themselves. Moreover, this study will help to facilitate access to this type of intervention for Spanish-speaking people, which is important due to the lack of options for many people who suffer from this problem, not only in Spain, but also in many countries in South America, in the United States, or in other countries with a significant number of Spanish-speaking citizens. The study will offer data that can be compared to those obtained in other studies carried out in English-speaking countries.

The data obtained in this study can be compared to results obtained in studies with DBT skills protocol programs for relatives. Several studies have found improvements in mental health patients’ relatives and the relationship with their loved ones, but further research is needed. One of the aims of this study is to examine the effect of the treatment components on increasing global family functioning and decreasing burden and distress, which will mean an important change in the research and treatment of relatives of people with BPD. To our knowledge, this is the first RCT study to compare FC to an active condition (TAU) and include a 6-month follow-up.

An important aim of the study is to identify methods to improve access to FC, as well as providing psychological support to everyone who needs it. We are living in a new era in the field of personality disorders, where BPD is given more and more attention. Researchers and clinicians are already crossing the barriers of traditional classifications and treatments, and we can now use these new protocols with significant and encouraging results. The use of the treatment in group format (a more cost-effective format than individual therapy) can help to disseminate and increase the access to these family interventions.

To conclude, in this study, the effectiveness of the application of the FC program will be tested by measuring the acceptability of this program and each specific module in relatives of patients with BPD.

An important strength of this study is that it is the first RCT of FC compared to an active intervention, and it is carried out in a routine clinical care context, an ecological setting. If the hypotheses are confirmed, we expect a fast implementation of FC in these centers and other similar settings. It is also the first study carried out in a Spanish-speaking population, thus facilitating the dissemination of the program in other Spanish-speaking countries or populations.

However, this study has some limitations. We do not expect to have recruitment difficulties because our research team collaborates with different clinical centers, but even so we would have liked to increase the number of centers participating in the study. This was not possible for funding and logistic reasons. Another limitation is that we included a follow-up at 6 months. We would have liked to carry out a long-term follow-up, but due to the conditions of the centers, it is difficult to contact relatives or patients who leave treatment or are discharged.

Finally, the aim of this study is to contribute to the literature on the efficacy of the FC program for relatives of people with BPD. We hope that this study contributes to the exploration of the efficacy and acceptability of programs designed to improve global family functioning and reduce family members’ burden. It will also contribute to improving our understanding of the relationships that may exist between the clinical evolution of the family members receiving the program and the evolution of the patients. If significant results are achieved, there will be an effect on the design and application of future family intervention programs, as a way to improve the overall functioning of the family climate and reduce the burden and distress they face. Finally, this study will allow the possible application of the program to Spanish-speaking populations in other countries.

## Data Availability

It is not possible to share the data because the study is in progress. We are now at the stage of data recruitment.

## Abbreviations

BPD: Borderline personality disorder
FC: Family connections
TAU: Treatment as usual
DBT: Dialectical behavior therapy
RCT: Randomized controlled trial
BAS: Burden assessment scale
FAD-GFS: Family assessment device-global functioning scale
DASS-21: Depression, anxiety and stress scale
FES: Family empowerment scale
QLI-Sp: Quality of life index-spanish version
OTSM: Opinion of treatment scales by modules
DERS: Difficulties in emotion regulation scale
LEAP: Lum emotional availability of parents
VIRS: Validating and invalidating responses scale
S-D: Socio-demographic
BL: Baseline
Post-T: Post-treatment
FU: Follow-up
MANOVA: Multivariate analysis of variance
ANOVA: Analysis of variance
